#### Secondary hypotheses

Compared to standard management, the implementation of a new EBF counselling intervention designed to support overweight woman will result in:
i)An increase in the volume of breast milk in ml as a result of an increase in serum prolactin levels in ng/ml, at 1 and 4 months.ii)Higher milk prolactin concentration and adequate macronutrient content of protein, lactose, fat and energy, at 1 and 4 months, which will in turn be associated with more optimal infant growth (based on WHO growth standards).

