### Secondary outcomes and variables

i)Maternal serum levels of prolactin and breast milk prolactin concentration and macronutrient content, measured at 1 and 4 months after delivery;ii)Estimated breast milk intake at 1 and 4 months according to WHO recommendations [53].

The study design is shown in Fig. 1 and a timeline of measurements in Fig. 2.

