#### Data collection

Data will be collected from all participants at five study time-points (last month of pregnancy, 24 h postpartum, and 1, 3 and 4 months postpartum) as described in Table 1. Questionnaires and assessments (detailed description below) will be completed at study visits as described in Figs. 1 and 2. The main information will be: i) sociodemographic and maternal and paternal health status questionnaire (last month of pregnancy); ii) maternal food consumption pattern measured using a maternal 24 h dietary recall [58, 59] and a semiquantitative food frequency questionnaire adapted for foods available in Colombia in a previous pilot study as described below; iii) maternal intention to breastfeed using the Infant Feeding Intention Scale adapted from the Nommsen-Rivers scale [60] (last month of pregnancy); iv) maternal risk of postpartum depression using the EPDS [54] (late gestation and 1 month postpartum); v) maternal physical activity using the IPAQ short version [61]; and vi) mother and infant anthropometric measurements. Breast milk macronutrient content will be determined at 1 and 4 months postpartum using infrared transmission spectroscopy (MIRIS Human Milk Analyzer) and serum and milk prolactin concentration will be determined by in vitro ELISA commercial kit.

**Table 1 Tab1:** Study variables and data collection questionnaires to be used in the study

Time-point	Questionnaire or assessment	Description
Last month of gestation	General information	Name, address, phone number, maternal ID, maternal date of birth, health social scheme.
	Maternal socioeconomic and demographic information	Marital status, socioeconomic level, type of housing, maternal occupation, monthly income, educational level, maternal leave, income assigned to food purchase, access to tap water, person in charge to infant, breastfeeding family support.
	Pregnancy information	Maternal smoking, obstetric background, gestational age, probable date of birth, supplement and vitamins intakes, laboratory reports, medical history.
	Paternal information	Educational level, monthly income, weight and height (self-reported), medical history.
	Intention to breastfeed	Five questions about intention to breastfeed or give formula until 6 months postpartum.
	Maternal anthropometry	Pregestational weight (self-reported), weight, height and MUAC measurements.
	Breast examination	Nipple and breast self-perception.
	Counselling assessment	Detected problems and concerted solutions.

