	Breast milk macronutrient content	Protein, lactose and fat content in human milk
	Prolactin in maternal serum	Concentration of prolactin hormone in maternal serum, 2 h after maternal wake up
3 months postpartum	Maternal anthropometry	Weight and MUAC.
	Infant anthropometry	Weight, length, head circumference, MUAC.
	Breast examination	Nipple and breast observation.
	Counselling registry	Detected problems and concerted solutions, applicability of last meeting’s concerted solution
	Infant 24-h recall	Time, place, type of food.
	Breast milk intake	Number of breastfeeds per day and night, time per each breastfeed, appetite (mother’s perception).
	Macronutrients content in breast milk	Protein, lactose and fat content in human milk.
	Prolactin in maternal serum	Concentration of prolactin hormone in maternal serum, 2 h after maternal wake up.
4 months postpartum	Maternal anthropometry	Weight and MUAC.
	Infant anthropometry	Weight, length, head circumference, MUAC.
	Breast examination	Nipple and breast observation.
	Assessment of breastfeeding counselling	Successful of new approach in EBF counselling with 5 questions to assess concerted solutions.
	IPAQ SV	Physical activity registry: type of activity, time (minutes per day), number of days per week.
	Maternal 24-h recall	Five steps 24HR: fast list, frequently forgotten foods, meals and time, food consumption in the last 24 h within detailed registry and standardized recipes.
	Semi-quantitative food frequency intake	Diary, weekly or monthly intake of 107 foods, included in 8 food groups.
	Infant 24-h recall	Time, place, infant feeding in the last 24 h (including breastfeeding, infant formula or other type of foods given to the baby).
	Breast milk intake	Number of breastfeeds per day and night, time per each breastfeed, appetite (mother’s perception).

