#### Measures

Questionnaires and assessments will be used to collect information among intervention and control groups at specific time-points, as shown in Table 1.
Maternal socioeconomic and demographic information, pregnancy information and paternal information: Information about residency, age, marital status, occupation, socioeconomic level, family size, family income, educational level, maternity leave, access to public services, social security, health benefits, smoking, alcohol consumption, family and medical history will be recorded. Gestational age will be determined by the date of the last menstruation, corroborated by sonographic studies available in the clinical notes. Paternal information will be reported by the woman and will include health status and monthly income.Intention to breastfeed: The scale uses five simple questions to determine the method of feeding that the woman plans for the baby. The scale has been validated and translated in previous studies [60].Maternal anthropometry: Anthropometric data - weight, height and mid upper arm circumference (MUAC) - will be collected in the last month of pregnancy, 24 h postpartum, and 1, 3 and 4 h months postpartum in minimal clothes. Weight will be measured in duplicate using an electronic scale (SECA 813, capacity 200 kg, precision 100 g), height measured in triplicate using a portable stadiometer (SECA 213, up to 205 cm) and MUAC measured in triplicate to the nearest cm (SECA 203 measuring tape, range 0 to 205 cm, graduation 1 mm). Weight gain during gestation (self-reported weight at the end of gestation minus pre-gestational weight) will be used as a baseline characteristic and as a covariate to predict the main outcomes.Breast examination: Participants will complete a questionnaire using illustrations of breasts to identify possible anatomical aspects that could make breastfeeding difficult (e.g. large breasts, flat nipples). This information will be used to focus the intervention for individual mothers.Edinburgh Postnatal Depression Scale (EPDS): This consists of 10 questions about feelings during the last week. It will be administered during the last month of gestation and 1 month postpartum as a tool to determine the risk of postpartum depression [54].Counselling register and evaluation: To assess the content of and adherence to the new EBF counselling intervention, a record of the problems identified will be kept during each visit. A questionnaire will also be administered by an independent investigator blinded to group allocation at the end of the study period (four months postpartum) which will include information on the problems identified, solutions and success, measured as: not successful (no problem resolution); limited success (partial resolution of the problem), or successful (problem solved).IPAQ short version: Physical activity questionnaire which considers types of physical activity, time (minutes per day) and number of days per week, and number of hours per day that the woman remains seated [61].Maternal food consumption: Determined using a standard food frequency questionnaire used and adapted in Colombian populations in other studies, and two multiple steps 24-h recall questionnaires to determine food consumption and nutrient intake including supplements, vitamins, minerals and maternal feeding problems; to be used as a baseline descriptive characteristic and as a potential confounder. This methodology is based on that described by the United States Department of Agriculture [58, 59]. To improve the quality of the data, photographs will be used to determine portion size [70]. Data analysis will be conducted using Colombian food composition tables [71], USDA standard nutrient reference database and food labels.Delivery information: Data about the type of delivery, newborn APGAR score, time of breastfeedng initiation, maternal-infant complications including those which delay the initiation of breastfeeding, and drugs administered during labour and the first 4 months after delivery.Newborn and infant anthropometry: Anthropometric variables - weight, length, MUAC and head circumference - will be measured by a trained nutritionist and dietitian following WHO protocol [72] at birth and 1, 3 and 4 months postpartum. Infant weight will be measured in duplicate using an electronic baby scale (TANITA 1583 with precision of 10 g, capacity 200 kg), length measured in triplicate using an infantometer (SECA 417, folding mechanism and foot stop, measuring range up to 100 cm), and head circumference and MUAC measured using a pediatric tape measure (SECA 201, range 0 to 205 cm, graduation 1 mm). Infant growth velocity will be defined as the change in the Z-score of weight for length, length for age, head circumference for age and mid upper arm circumference for age from birth to four months according to WHO growth standards [73]. Data collection will be performed by the same researcher in both groups to control information bias among observers.Breastfeeding information: This questionnaire collects information about initiation of breastfeeding at the hospital.Infant 24-h dietary recall: To determine the EBF prevalence, an infant 24-h recall will be used asking mothers about the foods consumed by the child during the previous day and infant feeding practices at 1, 3 and 4 months. = The counsellor will ask about the initiation, frequency and mode of preparation of specific beverages and semisolid foods or supplements since the last visit. This methodology will allow breastfeeding to be classified as exclusive or predominant according to WHO definitions [12].Breast-latching observation: Considers information about position of breastfeeding and maternal-infant perception of comfort during breastfeeding. This is a check-list that the investigator completes after watching a breastfeed [74].Breast milk macronutrients: Expression of breast milk (fore milk) will be performed at 1 and 4 months postpartum at the researcher’s office in the morning, using a Philips Single Electric Breast Pump under researcher supervision. The sample will be stored at − 20 °C in the laboratory at the Pontificia Universidad Javeriana for analysis. Content of macronutrients (carbohydrate, protein and fat) and energy in breast milk will be determined using the MIRIS Human Milk Analyzer, which uses infrared transmission spectroscopy and requires a human milk sample of 5 ml. Results will be recorded in the database.Breast milk prolactin: Determination of breast milk prolactin concentration will be performed using an Abcam ab226901 Human Prolactin SimpleStep ELISA kit. The procedure requires 2 ml of breast milk.Serum prolactin: To determine the maternal serum prolactin concentration, a non-probabilistic convenience subsample of 60 (20%) women will be selected. The blood sample will be taken at the laboratory of the institution, within 2 h of waking in the morning and before any food is consumed. The procedure will require 5 ml of maternal blood, which will be analyzed by ELISA (Abcam ab226901).

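### Table 1 schedules the milk and serum samples at 1 and 3 months, while the secondary hypotheses and outcomes set them at 1 and 4 months

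*Protocol article*

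**What the plan says.** The protocol article gives the timing of the milk and serum samples in several places.

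- **Secondary hypotheses.** Hypothesis (i) expects more milk "as a result of an increase in serum prolactin levels in ng/ml, at 1 and 4 months". Hypothesis (ii), on milk prolactin and macronutrients, names the same two months.
- **Secondary outcomes and variables.** Outcome (i) comprises serum prolactin, milk prolactin and "macronutrient content, measured at 1 and 4 months after delivery". Outcome (ii) is estimated milk intake, also at 1 and 4 months.
- **Data collection, text.** "Breast milk macronutrient content will be determined at 1 and 4 months postpartum". The prolactin clause in the same sentence gives no month of its own.
- **Measures.** "Expression of breast milk (fore milk) will be performed at 1 and 4 months postpartum". The entries for the milk prolactin and serum prolactin assays name no month.
- **Data collection, Table 1.** The 1-month block has "Breast milk macronutrient content" and a serum prolactin row described as "Concentration of prolactin hormone in maternal serum, 2 h after maternal wake up". The 3-month block has "Macronutrients content in breast milk" and a serum prolactin row with the same description. The 4-month block has no milk or serum sample.

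The Sample size section limits these laboratory measures to a subsample of 60 women, 30 per group.

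**The concern.** The Data collection section refers to Table 1 for what is collected at the five time-points, and the Measures section refers to it for when each instrument is used. It is therefore an operative schedule, and it orders samples at a different visit from the one that the outcomes require.

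A sample not taken at 4 months cannot be taken later. If staff or visit forms follow Table 1, secondary outcome (i) has no value at 4 months, which is also the trial's primary end-point. Milk intake would still be recorded then, but the 4-month link between milk volume and serum prolactin in secondary hypothesis (i) would lack its serum half. Values from 3 months, taken at a visit with a counselling session, might be used in their place. If both schedules are followed, women in the subsample give blood at 3 months for no stated outcome.

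**Working it through.** The plan gives no power or sample size figure that bears on this point, so there is nothing to reproduce. The check sets Table 1 against every statement of sampling time in the text.

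| Source in the protocol article | Macronutrients / milk sample | Milk prolactin | Serum prolactin |
|---|---|---|---|
| Secondary hypotheses | 1 and 4 months | 1 and 4 months | 1 and 4 months |
| Secondary outcomes and variables | 1 and 4 months | 1 and 4 months | 1 and 4 months |
| Data collection, text | 1 and 4 months | no month given | no month given |
| Measures | 1 and 4 months (milk expression) | no month given | no month given |
| Table 1 | 1 and 3 months | no row of its own | 1 and 3 months |

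**Step 1: is the difference an artefact of reading the table from PDF?** This is unlikely. The 3-month milk row is worded differently from the 1-month row ("Macronutrients content in breast milk" against "Breast milk macronutrient content"), so it is not a displaced copy. Both sample rows stand above the label that opens the 4-month block and follow rows that plainly belong to the 3-month visit.

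**Step 2: is there a sample elsewhere in the 4-month block?** The block has nine rows: maternal anthropometry, infant anthropometry, breast examination, the counselling assessment ("Successful of new approach in EBF counselling with 5 questions to assess concerted solutions"), physical activity, maternal dietary recall, food frequency, infant recall and breast milk intake. None is a milk or blood sample.

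**Step 3: which outcomes are touched?**

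- Outcome (i), the three laboratory measures: Table 1 provides no milk or serum sample at 4 months.
- Outcome (ii), estimated milk intake: the questionnaire row is present at 4 months.
- Primary outcomes: infant recall and maternal and infant anthropometry are all present at 4 months.

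**Step 4: size.** The subsample is 30 + 30 = 60 women. Under the text, up to 60 women give milk and serum at 4 months. Under Table 1, 0 of 60 do, and up to 60 give them at 3 months, a time for which no laboratory hypothesis or outcome is stated.

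**The case against.** The strongest reply is that the intended schedule is plain. The hypotheses, the outcomes, the macronutrient sentence and the milk-expression procedure all point to 1 and 4 months, and 3-month sampling appears nowhere except in two table rows. The natural explanation is that the rows were put in the wrong block. Nor does Table 1 alone run the visits: the Data collection section also refers to Figs. 1 and 2, and the caption of Fig. 2 presents it as the measurement timeline and includes the milk and serum samples. Those figures are not shown and may give the right months. The measures concerned are secondary and come from a subsample.

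Most of this stands as a limit on severity. It does not remove the contradiction: whatever the figures show, Table 1 and the outcome definitions cannot both be followed.

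Three stronger readings are tempting, and the document does not support them.

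- A reader might infer that all 4-month secondary outcomes would be lost. Estimated milk intake keeps its 4-month row, so only outcome (i) is exposed.
- A reader might count three analytes at two times and infer that four of six required measurements have no provision, because milk prolactin has no row. That counts an unlisted assay as a lost sample. Milk prolactin needs 2 ml of breast milk, and milk is collected at 1 month, so the 1-month value can come from that sample. The conflict concerns two sample types, milk and serum, at one visit.
- A reader might infer that every one of the text sections fixes prolactin at 1 and 4 months. The Data collection text and the Measures section name those months only for macronutrients and milk expression. The prolactin timing rests on the hypotheses and outcomes.

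**Conclusion.** The plan is wrong as written on this point. Table 1 places milk macronutrients and serum prolactin at 1 and 3 months and neither at 4 months, against the 1 and 4 months set by the secondary hypotheses and outcomes.

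If visits follow Table 1, secondary outcome (i) has 0 of 60 subsample women with a 4-month value, and the 3-month samples answer no stated question. That consequence is conditional. It assumes that visit forms were built from Table 1 and not from the text or the figures, and the document does not show which. It would go too far to say that the 4-month samples will certainly be lost.

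The primary outcomes, the sample size and the main analysis do not depend on the correction. This should be fixed, but it does not threaten the trial's main conclusions.

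**What to change.** - In Table 1, move the milk macronutrient row and the serum prolactin row from the 3-month block to the 4-month block, so that the table agrees with the secondary hypotheses, the secondary outcomes, the Data collection text and the Measures section.
- List milk prolactin with the milk sample at 1 and 4 months.
- State the months in the Measures entries for serum and milk prolactin, which now give none.
- Check that Figs. 1 and 2 and the visit forms show the same months.
- If samples have already been taken at 3 months, report them as 3-month values and do not pool them with 4-month values.

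The cost is the correction of one table and a check of the figures and forms. No samples are needed beyond those that the outcomes already require.

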### Breastfeeding counselling intervention

A new approach towards EBF counselling was designed based on Rogers’ Client-Centred Theory. The women assigned to the intervention group will receive the intervention at three key time-points: i) last month of gestation to prepare and promote the importance of early contact and breastfeeding initiation in the first hour postpartum, and to prepare the women for difficulties they may encounter in establishing breastfeeding; ii) 24 h postpartum to ensure that EBF is being established and to identify any difficulties the mother is experiencing; iii) early infancy (1 and 3 months postpartum) to identify breastfeeding problems and empower the women to continue exclusive breastfeeding. The intervention will be conducted by a certified breastfeeding counsellor with listening skills and an understanding of the particular problems faced by overweight women during breastfeeding, who will analyse the environment and maternal breastfeeding problems in order to reach consensus solutions with the woman.

#### New EBF counselling intervention

For the purpose of this study, EBF counselling for overweight women is defined as a well-structured and permissive relationship built on trust between the counsellor and the pregnant and breastfeeding woman, using her feelings, beliefs and sociocultural environment to gain an understanding of herself and her situation in order to empower the woman and achieve EBF for six months.

#### Intervention theoretical framework

Based on Carl Rogers’ Client-Centred Theory [62], this intervention will have three main principles: i) dialogue between counsellor and woman in an atmosphere of respect for her individuality and particular situation related to breastfeeding; ii) empowerment of the woman, raising awareness to allow her to choose the best alternative to achieve her goals for EBF; and iii) concerted solutions under the guidance of the counsellor who will give a set of alternatives to solve problems related to breastfeeding at critical moments, which will be mainly, but not exclusively, mechanical problems and/or technical problems with breast milk production.

#### Essential time-points for intervention

Three key time-points to intervene were identified to increase the duration of EBF in overweight women, according to their particular needs [63]: i) the last month of gestation as the moment to identify mechanical problems such as larger breasts and flattened nipples [64] and the intentions and fears of the women regarding breastfeeding [65], to promote the importance of early contact (skin to skin) between the women-infant dyad [66] and initiation of breastfeeding in the first hour postpartum [67], and to prepare the women to recognize adequate infant latch-on; ii) 24 h postpartum to evaluate suckling, early initiation of breastfeeding and beginning of lactogenesis II [68]; iii) early infancy (1 and 3 months postpartum) to empower the women in the continuation of EBF (periods where there is a risk of early weaning) [69]. During each counselling session, counselling support materials with key messages will be given to the women to reinforce counselling. Counselling will be evaluated at every time-point using a structured questionnaire about maternal satisfaction and usefulness. Adherence to EBF will be assessed by asking the mother if she has exclusively breastfed during the last 24 h at each time-point.

Women with breastfeeding difficulties at the time of the intervention that are beyond the scope of the researcher’s competence will be referred to the relevant professional so that appropriate treatment can be offered to promote continued breastfeeding (e.g. physician, nurse, psychologist). Referrals and the reason for the consultation will be recorded and compared between groups.

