## Methods

### Study design

A two-arm randomized controlled trial was designed to identify the effect of a new EBF counselling intervention specifically designed to support overweight women, on the prevalence of breastfeeding and EBF, infant growth velocity and maternal postpartum weight loss up to 4 months. Although the primary end-point will be 4 months after delivery, mothers will be advised to continue EBF until 6 months, as recommended by WHO.

The trial involves overweight women recruited in the last month of pregnancy and their infants. Eligible overweight women will be randomly assigned to an intervention or control group and outcomes will be measured from birth and up to 4 months after delivery. The control group will receive standard counselling from Baby Friendly Hospitals, while the intervention group will receive the new EBF counselling intervention for overweight women. The intervention will be carried out at three time-points:
i)Last month of pregnancy.ii)24 h postpartum.iii)Early infancy (1 and 3 months postpartum).

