#### Standard counselling

This will be performed in the control group, based on the institutional and national policy for breastfeeding (Resolution 412 of the year 2000). During pregnancy, women receive a group talk about the importance of breastfeeding as part of the maternity preparation course at the institution. During labour, early contact and early initiation of breastfeeding is supported by health workers at the institution who identify the risks for the woman-child dyad. During hospital discharge, women receive nutritional recommendations with an emphasis on EBF during the first 6 months. During the first 4 months postpartum, the follow-up time of the study, it is estimated that women in the control group will attend two follow-up growth and development visits, where the weight and length of the child is evaluated and breastfeeding support is given by group activities or individual consultation carried out by health professionals. The intervention group will also receive this standard follow up, as well as the new approach in EBF counselling. Table 2 summarizes the main characteristics of the new approach compared with the standard counselling given by the institution.

**Table 2 Tab2:** Time-points and description of breastfeeding counselling among control and intervention groups

Time-point	Intervention group		Control group	
	Issues to follow	Responsible	Standard care	Responsible
Last month of gestation	1. Dialogue with the women to determine risk of possible breastfeeding problems: - Fears and expectations - Breast examination - Breastfeeding problems - Intention to breastfeed 2. Maternal empowerment - Knowledge of familiar and social environment - Motivation - Early contact (skin to skin contact) - Commitment 3. Agreed solutions - Individuality respect - Realistic and assertive solutions	Researcher	Information on the benefits of breastfeeding and breastfeeding positions through a one-hour group talk as part of the institution’s course on preparation for motherhood.	Nursing Department

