24 h postpartum	1. Dialogue with the women to evaluate problems and difficulties identified at gestation: - Fears and expectations - Early breastfeeding - Skin to skin contact - Adequate latching and suckling - Human milk volume 2. Maternal empowerment - Breastfeeding crisis: fatigue, fears and worries. - Motivation 3. Agreed solutions - Respect for individuality - Realistic and assertive solutions.	Researcher	Institutional policy to allow rooming in, skin to skin contact. Risks of early weaning. Nutritional recommendations about breastfeeding importance at hospital discharge.	Institutional health care professionals
1 month postpartum	1. Dialogue with the women to follow up the agreed solutions and identify new difficulties with breastfeeding - Maternal perception of milk volume produced - Maternal perception of infant appetite 2. Maternal empowerment - Fears and expectations: low breast milk volume - Motivation and solutions follow up - Self-esteem 3. Agreed solutions - Individuality respect - Solutions follow up and measure of breastfeeding achievements	Researcher	Six visits during the first 12 months to follow up infant growth and development. It includes education in breastfeeding in group meetings. Breastfeeding counselling on demand or by referral.	Institutional health care professionals: Nurse Department
3 months postpartum	1. Dialogue with the women to follow up agreed solutions and identify new breastfeeding difficulties: - Back to work, study and other activities. - Early initiation of complementary food 2. Maternal empowerment - Fears and expectations - Motivation and follow up of solutions - Self-esteem 3. Agreed solutions - Individuality respect - Solutions follow up and measure of breastfeeding achievements	Researcher	Six visits during the first 12mo to follow up infant growth and development. Lack of adherence to the program.	Institutional health care professionals, Prevention and promotion programs at the institution.

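### The planned between-group comparison of referrals rests on unequal detection and recording in the two arms

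*Protocol article*

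**What the plan says.** The referral rule stands in the description of the intervention, under Essential time-points for intervention. It concerns "Women with breastfeeding difficulties at the time of the intervention that are beyond the scope of the" researcher's competence, and sends these women to a suitable professional. The next sentence commits the plan to a comparison: "Referrals and the reason for the consultation will be recorded and compared between groups".

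Study design assigns the sessions to one arm: "The control group will receive standard counselling from Baby Friendly Hospitals, while the intervention group will receive the new EBF counselling intervention for overweight women". In Table 2 the researcher is responsible for every intervention session, and each session includes a dialogue to find or follow up breastfeeding problems. For control women the responsible parties are the nursing department and other institutional staff. Their 1-month entry includes "Breastfeeding counselling on demand or by referral". The Standard counselling text adds that at routine follow-up visits "breastfeeding support is given by group activities or individual consultation carried out by health professionals". It expects two such visits in the first 4 months, and notes that "The intervention group will also receive this standard follow up, as well as the new approach in EBF counselling".

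The Data collection and Measures sections say that all participants are seen at five time-points and that the same researcher collects data in both groups.

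**The concern.** The two adjacent referral sentences do not fit together as worded. The first ties the trigger to the time of the intervention, which one arm receives. The second assumes counts that can be compared across both arms. The article does not say how a control woman's problem would come under the rule, or where her consultation through standard care would be written down.

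If problems are sought at every session in one arm and surface mainly when the mother asks in the other, the arms can differ in recorded referrals while having problems equally often. A reader of the results could then take an excess in the intervention arm as a sign that counselling brings more difficulties, or a low control count as a sign that those women had few.

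**Working it through.** The protocol states no figure for referrals, so there is nothing to reproduce. The check sets the relevant places side by side and follows what a count would measure.

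**1. Where a problem can be found**

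| | Intervention arm | Control arm |
|---|---|---|
| Counselling sessions with the researcher (Study design, Table 2) | Last month of pregnancy, 24 h, 1 month, 3 months | None |
| Standard care (Standard counselling, Table 2) | Yes, in addition | Yes: group talk, support around delivery, about two follow-up visits by 4 months, help on demand or by referral |
| Study data visits (Data collection, Measures) | All five time-points | All five time-points, same researcher |
| Stated study referral rule | Yes, at the time of the intervention | Not stated |

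Standard care and the data visits are shared. What differs is the four sessions and the referral rule attached to them.

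**2. Where a referral can be recorded**

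- The counselling registry in Table 1 lists problems and agreed solutions. Measures says that Table 1 instruments are used in both groups, but gives the purpose of the visit-by-visit problem record as assessing the content of, and adherence to, the new counselling. Whether it is completed for control women is unclear.
- Table 1 also has breastfeeding difficulties and latch observation at 24 h, and breast examination at some visits. These describe problems, not consultations with other professionals.
- The independent questionnaire at 4 months goes to all mothers who completed follow-up (Data management). Its described content is problems, solutions and success. Referrals and consultations are not named.

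So no Table 1 item is described as capturing a control woman's consultation or referral through standard care.

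**3. What the comparison would then measure**

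For one arm, write the expected number of recorded referrals as

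recorded = N × λ × d × r,

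where N is the number of women, λ the rate of problems needing another professional, d the probability that such a problem is detected and referred, and r the probability that the referral is recorded. With 145 women planned per arm, N cancels, and the ratio between arms is

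(λ_I / λ_C) × (d_I / d_C) × (r_I / r_C).

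If problems are equally frequent, λ_I / λ_C = 1, and the observed ratio is (d_I × r_I) / (d_C × r_C). Step 1 gives reason to expect d_I > d_C, and step 2 gives reason to expect r_I > r_C. The ratio would then exceed 1 without any difference in problems. The protocol gives no value for λ, d or r, so the size cannot be calculated, and none is assumed here.

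**The case against.** The strongest reply is that the comparison sentence itself implies recording in both arms, and that the time of the intervention can be read as the study time-points, which both arms share. Control women have individual consultation and referral under standard care, the same researcher meets them at the data visits, and Data management speaks of counselling visits for both groups. An independent investigator, described in Measures as blinded to allocation, questions all mothers who complete follow-up. Finding more problems is also part of what this counselling does, so more referrals could be a genuine effect of it.

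Much of this stands. A reader might infer that referrals can arise in the intervention arm only, so that the control count is zero by design. The documents do not support that, for the reasons just given. The reply does not settle which reading of the referral sentence is meant, and the two readings produce different data. Nor does it supply a described item that records consultations alike in both arms.

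A reader might also infer that a raised depression score at 1 month leads to no action. The article says only that the scale is used "as a tool to determine the risk of postpartum depression" and is silent on handling. A condensed article may leave that to the full protocol, so it forms no part of this point.

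**Conclusion.** The concern holds as one of unequal ascertainment and an unclear rule for control women. A between-group difference in referrals would mix how often problems occur, how actively they are sought and how reliably they are recorded. The likely direction is towards more recorded referrals in the intervention arm; the size is unknown.

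This rests on two assumptions: that the sessions uncover problems which routine care or data visits would not, and that the full study forms contain no common item on consultations beyond those the article describes.

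The consequence is limited. Referrals are not among the listed primary or secondary outcomes, and the article does not present them as a harm measure. The conclusions on exclusive breastfeeding, infant growth and maternal weight loss are not affected. The point deserves correction because the plan commits to this comparison and the remedy is small.

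**What to change.** 1. Reconcile the two referral sentences by stating whether and how the rule applies to control women at the shared study visits. Any clinical criteria remain with the sponsor and the site.
2. Base the between-group comparison on one identically worded question to every mother in both arms at 1, 3 and 4 months: any consultation or referral for breastfeeding problems since the last visit, and the reason.
3. Report referrals made by the researcher during counselling sessions separately, for the intervention arm, as description only.

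The cost is one extra question on three existing visit forms and a short wording change. The common question evens out recording. It does not remove consultations that the sessions themselves prompted, so the result should be described as use of help, not as frequency of problems.
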